### Maternal Vulnerability Segmentation Tool

A vulnerability screening tool was developed to identify pregnant women with heightened vulnerabilities. We performed logistic regression analyses using the 2019 Ethiopian Demographic and Health Survey to identify factors associated with ANC attendance and institutional delivery. Next, a multivariate cluster analysis (K-medoids) was conducted to evaluate the tool’s ability to classify pregnant women as having low, moderate, or high vulnerability. The initial validation of the tool was conducted through expert reviews and group discussions with healthcare workers. Feedback from these stakeholders helped evaluate whether the screening items were comprehensive and relevant to women living in the study areas. The tool was then pretested with the target group of pregnant women to ensure its clarity and applicability. This process allowed us to refine the questions and incorporate illustrations to enhance understanding among rural communities.

The final screening tool included 20 items assessing individual, social, structural, and service-level determinants. Women who scored less than 12 were classified as having low vulnerability, those scoring 12–15 as moderate, and those scoring greater than 16 as highly vulnerable. Thus, an aggregate score of 12 or more indicated moderate to high vulnerability. These cutoffs were determined as ANC and health facility delivery were lower among pregnant women with moderate and high vulnerability scores compared to those with low vulnerability scores.

### Recruitment

After obtaining a list of all interested women from health extension workers and health development armies, data collectors visit the women in person to screen their pregnancy status and vulnerability level to assess their eligibility. With the woman’s verbal consent, the data collector administers the pregnancy screening tool to identify her pregnancy status. Only women at 5+ months of pregnancy and aged 15–49 are considered eligible. If eligible, she is screened for her vulnerability level, assessed through the vulnerability screening tool. Those considered to be moderately to highly vulnerable are eligible and entered into the sampling frame. Women who score at least 9 out of the maximum 20 vulnerability screening questions will be identified as a study participant. All responses to the screening questions will be entered into the data collectors’ mobile phone application that automatically determines pregnant women’s eligibility during the visit. 

All eligible women are entered into our sampling frame. After listing eligible pregnant women, we aim to recruit approximately three women per enumeration area to achieve our target sample size. If an enumeration area has five or fewer eligible women, they are all contacted for recruitment. If there are more pregnant women than the minimum required number of pregnant women, we randomly select the required number. If a woman is not interested or available for participation, we contact the next randomly selected woman for recruitment. Recruitment continues until our sample size is reached, expanding to other enumeration areas if necessary. Recruitment in Phase 1 was completed in this way, and Phase 2 recruitment will follow this procedure.

For the qualitative assessment, recently delivered women who receive our intervention and health workers in the intervention sites are purposively recruited. Purposive selection of the sample allows us to understand the experiences of engaging in our implementation process among diverse individuals. For women, the selection criteria include: 1) residing in Siraro and Shalla woredas, 2) being exposed to the HCD solutions during their last pregnancy, and 3) having delivered after receiving the solutions. To further obtain diverse and in-depth experiences among our sample, we prioritize recruiting women who are in earlier gestational ages (5
^th^ month or earlier) at the time of recruitment (before intervention), as those in late pregnancy terms may not be fully exposed to our solutions. Also, both women who delivered in health facilities and at home are contacted for recruitment to capture a broad range of experiences. We also attempt to ensure diversity in kebeles and primary health care units in the selected sample to ascertain potential differences. The criteria for recruiting health workers include: 1) those working in Siraro and Shalla woredas, 2) serving as a health extension worker, health development army, primary health care unit (PHCU) staff in the woreda, or health officials such as woreda health leaders, and 3) being engaged in the implementation of the HCD solutions. Trained data collectors administer consent and interview with eligible pregnant women at their homes and with health workers at their workplaces (e.g., local health center). We will use the same sampling approach for both midline and end-line qualitative assessments. 

### Data collection and measurement

**
*Survey interview*.** All participants from Phases 1 and 2 undergo a one-on-one survey interview to assess sociodemographic information, psychological factors, social and structural factors, and maternal health service utilization. A structured interview is administered by a local data collector in the local language. The survey captures the self-reported place of the most recent childbirth along with uptake and frequency of ANC visits during the most recent pregnancy. Secondary outcomes include knowledge, attitudes, and perceptions about maternal health service utilization, social norms, gender norms, spousal dynamics, decision-making, and community and structural factors. Midline (post-intervention in Phase 1) and end-line (post-intervention in Phase 2) assessments additionally include questions measuring program exposure.

**
*Qualitative interview*.** Purposively selected women from the study participants (n=20) along with health workers (n=32) engaged in the program participate in an in-depth interview. Given the 4-month duration of program implementation among pregnant women in their 5
^th^ or higher months of pregnancy, interviews are administered to recently delivered women inquiring about their perceived effects of the intervention on the place of childbirth and ANC uptake during pregnancy. Additionally, the interview guides for women and health workers contain questions around key implementation research outcomes, including acceptability and feasibility, to identify any similarities and differences arising across different types of interview participants.

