^. Under these national goals, providing pregnant women with essential maternal health services, including institutional delivery (i.e., childbirth in health facilities attended by skilled birth attendants), antenatal care (ANC), and iron and folic acid supplementation, has been a key strategy for optimizing maternal and child health outcomes in Ethiopia. These maternal health services can significantly reduce the risk of maternal, perinatal and neonatal mortality in low- and middle-income countries and alleviate health disparities worldwide
^
7–
9
^.

Nevertheless, there remains an urgent need to address disproportionate uptake of and access to maternal health services in Ethiopia. Taking institutional delivery coverage as an example, women’s use of health facilities for childbirth greatly varies by region and sociodemographic characteristics. With the national average being approximately 48%, the percentage of institutional delivery use ranges from 23.3% in Somali Region to 94.8% in Addis Ababa, the capital city
^
3
^. Also, 79% of women in the lowest wealth quintile delivered a baby at home; the corresponding figure for women in the highest wealth quintile was 14%. Parity is also associated with home delivery: women having six or more births are more likely to deliver at home, compared to those delivering for the first time.

Prior evidence suggests that women’s use of maternal health services is shaped by multiple factors at the socio-ecological continuum. Barriers to maternal health service uptake among pregnant women reside at multiple levels, including at the individual level (having poor knowledge of obstetric complications and danger signs, low risk perceptions, high parity, and no birth preparedness plans)
^
10–
12
^, social level (social and gender norms, support from family, decision-making power)
^
11,
13,
14
^, cultural level (respect for elders, perception about pregnancy-related matters as women’s privacy, relationship with traditional birth attendants in the community)
^
3,
15–
17
^, structural level (distance to health facilities, transportation and road infrastructure, costs for traveling, delivery cost)
^
11,
15,
18
^, and those that are service-related (lack of services that respect women’s privacy and preferences, disrespectful treatment by health workers, and staff and medical supply shortages)
^
10,
15,
19,
20
^.

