### Study design

A community-based quasi-experimental study design was chosen to assess differences in key variables between the intervention and control arms. We chose a quasi-experimental design for several reasons. We lacked information about clear randomization unit given the characteristics of individuals or clusters (woredas), and it was likely that many woredas in Oromia region are not homogenous towards our outcomes of interest. Another reason was due to resource constraints, as we did not have a sufficient number of woredas in our study to conduct a pure randomized trial design. The study included two waves of data collection from a panel of recruited pregnant women at Phase 1. We attempt to leverage Phase 1 findings to inform the development of study tools and identify factors affecting implementation to provide insights into the improvement our intervention at Phase 2. This study is registered at ClinicalTrial.gov (NCT05907720).

In Phase 1, we conducted the baseline survey with 470 pregnant women enrolled in intervention and control arms in January 2024. After the baseline survey, we implemented a set of HCD prototype solutions in the intervention arm only, keeping the usual standard of care intact in the control arm. After the 4-month period of HCD solution implementation, we conducted the midline survey among the same women in the panel from both the intervention and control arms. In the midline survey, we interviewed 453 pregnant women, with 17 pregnant women lost to follow-up. The midline assessment also included in-depth interviews with purposively selected pregnant women from the panel and health workers who engaged in implementation.

In Phase 2, we will conduct a post-only study with a new sample of vulnerable pregnant women who will be recruited after the implementation of refined HCD solutions. Since the focus is on enhancing implementation feasibility, scalability, and health system ownership of Phase 1 solutions, which have already shown significant improvements in institutional delivery, we believe a post-only assessment is sufficient to observe consistent effectiveness. 

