### Sample

Our primary target participants are vulnerable pregnant women aged 15–49. For consent administration, we segmented adult pregnant women aged 19 and above, pregnant adolescent girls aged 15–18, and service providers. Service providers, such as midwives, health extension workers and health development armies who had engaged in the study were recruited for qualitative assessment at midline (Phase 1) and will be enrolled in end-line (Phase 2).
Table 1 below summarizes inclusion and exclusion criteria for each sample population.

**Table 1. T1:** Summary of inclusion and exclusion criteria of study sample.

Respondent type	Inclusion criteria	Exclusion criteria
Pregnant women	Women in their 5th or higher months of pregnancy; meet the high vulnerability criteria.	Pregnant women who are less than 5 months pregnant; meet the low vulnerability criteria.
Women who delivered recently (Midline and end-line only)	Recently delivered women included in the panel for baseline assessments during Phase 1; those who have received HCD solutions during Phase 2; meet the high vulnerability criteria.	Recently delivered women who were not included in the panel; did not have exposure to HCD solutions; meet the low vulnerability criteria.
Heath Extension Workers	Who work in health promotion and essential maternal health services in heath posts.	Who have worked in this position less than 6 months in the intervention arm.
Health Development Armies	Community volunteers who work on early screening and health promotion activities for pregnant women.	Who have worked in this position less than 6 months in the intervention arm.
Head of woreda health office	Head/Vice Head of the woreda Health Office who help facilitate implementation of the project	Who have worked in this position less than 6 months in the intervention arm.

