### Implementation plan

As part of the implementation of the interventions in Phase 1, the study team conducted an orientation training for health extensions workers and health development armies (known as Hadha Gare locally) to equip them with the skills needed to identify vulnerable pregnant women using a vulnerability screening tool and to effectively implement the solutions. The prototype solutions were delivered by the trained health development army with the help of health extension workers for a duration of four months from February to May 2024.

Prior to implementation, the health development army identified vulnerable pregnant women within their catchment area. They then scheduled an appointment to facilitate family discussions about the prototype solutions. The audio programs and print materials were intended to be delivered throughout five home visits by the health development army. For women whose gestational age was high (8–9 months), we aimed to provide audio and print materials on institutional delivery through three home visits.

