Nevertheless, this study will use a multi-level modeling framework to assess the intervention effect based on a difference-in-difference analysis by computing differences between baseline and midline within each arm, and then test this difference between intervention and control arms. A fixed effects model will first be used to observe this effect of the intervention. Kebele and PHCU will then be included as random intercepts to account for clustering within these levels. The estimated variance for random effects will show the amount of variability in the outcome that is explained by the clusters (i.e., how much of institutional delivery uptake is attributed to a kebele). If the coefficient of the interaction term is significant with the significant model fit, we will observe significant program effects. The identical analyses will be conducted with 4+ANC visits as the outcome variable. Other covariates will be included by comparing goodness-of-fit statistics (e.g., AIC, BIC) to improve the model fit. Proper model specification and diagnostic tests will be conducted to enhance the robustness of the results. Phase 2 data analysis will focus on comparing service utilization between intervention and control arms. Since we expect that study effectiveness will be stronger in Phase 2 with the implementation of enhanced solutions, we will also compare the study outcomes with baseline at Phase 1.

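### Phase 1 difference-in-difference: the baseline outcome is an earlier birth, which first-time mothers do not have, and the baseline pregnancy for 4+ ANC is undefined

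*Protocol article*

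**What the plan says.** **Measure.** Under Data collection and measurement, for participants of both phases: "The survey captures the self-reported place of the most recent childbirth along with uptake and frequency of ANC visits during the most recent pregnancy".

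**Who is measured at baseline.** Study design: "we conducted the baseline survey with 470 pregnant women enrolled in intervention and control arms in January 2024". Recruitment: "Only women at 5+ months of pregnancy and aged 15–49 are considered eligible". No parity criterion is stated, and the Sample section includes "pregnant adolescent girls aged 15–18".

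**Who is measured at midline.** The same panel. Table 1 describes these respondents as recently delivered. Study design still calls the 453 women interviewed pregnant and reports 17 lost to follow-up.

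**Analysis.** The Data analysis plan specifies a multi-level difference-in-difference by "computing differences between baseline and midline within each arm, and then test this difference between intervention and control arms", with random intercepts for kebele and PHCU. A significant interaction term is read as a program effect. For the second outcome: "The identical analyses will be conducted with 4+ANC visits as the outcome variable". Arms are first compared on potential confounders, and observed differences are controlled for. Further covariates enter by goodness of fit.

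**Parity.** The Introduction says that "women having six or more births are more likely to deliver at home, compared to those delivering for the first time".

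**The concern.** A before-and-after contrast in a panel is easiest to read when the same quantity is measured twice in the same women. Here the women are the same, but the birth is not: a previous birth is subtracted from the index birth. For a first-time mother there is nothing to subtract.

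Nothing in the model as written makes both waves hold the same women. It has no woman-level term and no stated restriction to women with both values. If first-time mothers are simply missing at baseline and present at midline, the make-up of each arm changes between waves, and the interaction term absorbs any difference between arms in that change. The woredas were not randomised, so equal shares of first-time mothers cannot be presumed.

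For 4+ ANC there is a further question: which pregnancy a woman already five or more months pregnant is asked about. The result matters beyond Phase 1, because the article uses the Phase 1 improvement in institutional delivery to justify a post-only Phase 2 and plans to compare end-line with this same baseline.

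**Working it through.** **1. What each wave records**

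| | Baseline (5+ months pregnant) | Midline (delivered, per Table 1) |
|---|---|---|
| Delivery, woman with an earlier birth | previous birth | index birth |
| Delivery, first-time mother | no value | index birth |
| ANC, if the current pregnancy is meant | index pregnancy, unfinished | index pregnancy, complete |
| ANC, if the previous pregnancy is meant | previous pregnancy; no value for first-time mothers with no earlier pregnancy | index pregnancy, complete |

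A woman not yet delivered at midline would report the same earlier birth twice. The article does not say whether there were any.

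**2. Composition bias, institutional delivery (linear scale)**

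Let f be an arm's share of first-time mothers and g the gap in facility delivery between them and other women. If they are present at midline only, the arm's midline proportion is p + f·g, where p is the proportion in women with an earlier birth. The baseline proportion contains no such term. With no program effect and parallel trends in women with an earlier birth, the difference-in-difference equals

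(f_intervention − f_control) × g.

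The documents give neither f nor g, so the inputs are assumed: a share difference of 5 to 10 points and a gap of 20 to 40 points.

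- Low: 0.05 × 0.20 = 0.01, or 1 point.
- High: 0.10 × 0.40 = 0.04, or 4 points.

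The target in Sample size calculation is 9% beyond 48%, read here as 9 percentage points. If the shares are equal, or first-time mothers are left out of the contrast, this bias is zero.

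**3. Gestational-age cut-off, 4+ ANC (only if the current pregnancy is meant)**

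Assume that the chance of having reached four visits rises by 7.5 points per gestational month, and that the arms differ by half a month at enrolment. Baseline then shifts by 0.5 × 7.5 = 3.75, about 4 points, in one arm, and midline does not shift. Gestational age at enrolment, G, has the same value at both waves. A main-effect term e·G therefore cancels when baseline is subtracted from midline and leaves the shift in place. Removing it would take a term that lets G act differently by wave, which the article does not mention.

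**4. What restriction would cost in precision**

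Stated inputs are 48%, a 9-point effect, 80% power, alpha 0.05 (two-sided assumed) and ICC 0.009. With v0 = 0.48 × 0.52 = 0.2496, v1 = 0.57 × 0.43 = 0.2451 and within-woman correlation ρ:

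n per arm = (1.96 + 0.842)² × [2·v0·(1 − ρ) + v0 + v1 − 2ρ√(v0·v1)] / 0.09².

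This gives 964 at ρ = 0, 482 at 0.5 and 241 at 0.75. The stated 240 per arm thus matches this formula only with a correlation near 0.75, which the article does not give. That does not show 240 to be wrong, but so high a correlation across different pregnancies needs justification.

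For power, take 453/2, about 226 per arm (equal split assumed), and divide by the design effect 1 + 2 × 0.009 = 1.018 for three women per area, giving 222. The share of first-time mothers is assumed.

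| Share without baseline value | Women per arm | Power, ρ = 0.75 | Power, ρ = 0.5 |
|---|---|---|---|
| 0% | 226 | 77% | 48% |
| 10% | 203 | 72% | 44% |
| 20% | 181 | 67% | 40% |
| 30% | 158 | 61% | 36% |

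**The case against.** The best defence has four parts.

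*A previous-birth baseline can be legitimate.* An arm-level difference-in-difference is valid if trends from one birth to the next are parallel across arms. That is correct, and the design should not be called invalid. The assumption is, however, neither stated nor defended.

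*The article does not say that first-time mothers enter at midline only.* Also correct. A reader might infer it from the model, but they could be dropped, and the plan promises to examine missingness and choose a remedy. What stands is that the estimator as written allows midline-only entry, and that the missing value is structural: no questionnaire can supply an earlier birth.

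*The plan adjusts for arm differences.* It does, and woredas with similar service uptake were sought, so it would be wrong to say that nothing protects the contrast. Adjusting for parity can reduce the composition bias. But adjustment depends on an observed difference, parity is not named, and a main effect may not cure the gestational-age problem.

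*The ANC point depends on a questionnaire not shown.* This stands in part. A reader might conclude that the baseline ANC count is certainly that of the current pregnancy and hence mechanically low. The text does not establish that; the last completed pregnancy is also a possible reading. Neither reading, though, makes identical analyses sound without a definition.

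The Introduction's parity statement compares first births with six or more, so it supports a direction and not a 20 to 40 point gap. High parity is also listed among the vulnerability drivers behind the screening tool, so first-time mothers may be few.

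**Conclusion.** The concern holds, as a mismatch between the stated measure and the stated estimator rather than as missing detail. For institutional delivery it follows from the article's own text: the baseline value belongs to an earlier birth and is absent for first-time mothers, whom no stated criterion excludes. The resulting bias is possible but of unknown size. The range of 1 to 4 points rests wholly on assumed shares and gaps, and on first-time mothers contributing at midline only. For 4+ ANC the finding is an ambiguity with a problem on either reading; the 4-point illustration applies only to the current-pregnancy reading.

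Two stronger readings should be resisted. The interaction term is not the study's only test: Phase 2 compares arms directly at end-line, and that comparison is unaffected, although the planned comparison of end-line with the Phase 1 baseline does inherit the mismatch. Nor is it an error to count women enrolled at 8–9 months in the ANC effect. For them the article says "we aimed to provide audio and print materials on institutional delivery through three home visits", so a reader might want them removed or reported apart. Keeping all enrolled women is a defensible choice that mainly dilutes the effect, and separate reporting is optional.

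**What to change.** 1. State which birth and which pregnancy each outcome refers to at baseline and at midline, and how women without an earlier birth are handled.
2. Institutional delivery: run the difference-in-difference in women with a previous birth and a delivered index pregnancy, and state the assumption of parallel between-birth trends. Report beside it a midline arm comparison in all delivered women, adjusted for pre-intervention covariates including parity.
3. 4+ ANC: do not difference against an unfinished pregnancy. If baseline recorded the current pregnancy, compare index-pregnancy visits between arms at midline, adjusting for gestational age at enrolment and, where recorded, visits already made by then. If baseline recorded the previous pregnancy, proceed as for delivery.
4. Label the change as made after Phase 1 data collection. Study status places Phase 1 at the analysis stage, and the article already describes its delivery result as significant.

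The cost is mainly analysis wording. Gestation was screened at recruitment, but the article does not show that index-pregnancy visits were recorded at baseline, so that adjustment may be unavailable. Fewer women enter the difference-in-difference. With an assumed 10 to 30% of first-time mothers and a correlation of 0.75, power falls from about 77% to between 72% and 61%, and further if some women were undelivered at midline.
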